### Softwares

Qualitative analyses will be carried out in Nvivo v.11. Joint analyses will be generated in excel or in Nvivo v.11. All quantitative analyses will be carried out in Stata 17.

### Data and safety monitoring

A formal safety review process will be implemented for the duration of the study which will include a data and safety monitoring board of three individuals with expertise in clinical obstetrics, biostatistics, and medical ethics not affiliated with the study. Formal DSMB meetings will occur every six months, and ad-hoc meetings may be convened. At DSMB review, or any other time, the DSMB may recommend that the study proceed as designed, proceed with design modifications, or be discontinued. Study investigators will routinely review participant safety data during their weekly team meetings and will convene on an ad hoc basis to make decisions regarding the handling of any significant safety concerns in conjunction with the DSMB. If necessary, experts external to the investigative team or the DSMB with expertise in the appropriate areas may be invited to join safety review activities.

Interim analyses will be carried out by the study data manager for DSMB review formally halfway through the clinic-based assessment phase data collection, i.e., when 50 study participants have completed the study. Findings from the pilot period will be used to inform potential modifications to data collection or other study procedures. Interim analysis of efficacy data when about half the study events are recorded, using stringent rules for stopping the trial early in case of positive effect. Interim trial data will be kept confidential and restricted to the DSMB, except if early stopping of the trial is advised. In addition to recommendations from the DSMB, the study team will seek the input of the Community Advisory Board to help inform decisions about modifications to improve study rigor and appropriateness, among other aspects.

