Insertable devices, or technologies that reside within the body, have many applications to improve women’s health and quality of life [27, 28]. An insertable vaginal cup is an acceptable, safe, and effective solution for preventing leakage of menstrual blood and eliminating odor among women and girls worldwide including settings where fistula is prevalent [29–33]. Incidental findings in case reports suggest the utility of the menstrual cup for control of urine leakage in women with fistula [34–36] however, no systematic evaluation of the effectiveness of the cup within a fistula-endemic setting has been conducted. The cup is durable, reusable, and low-cost in addition to being concealable to prevent additional stigma burden. It sits low in the vagina, and thus is suitable for collecting leakage for selected vesicovaginal fistulas (VVF). Urine is emptied from the cup after removal or via valve release while inserted.

Our collaborative team of physicians and researchers from University of Ghana and New York University were the first to systematically evaluate efficacy and acceptability of an insertablevaginal cup for short-term vesicovaginal fistula management at a health facility in Ghana within a feasibility study [37, 38]. The mean leakage reduction with cup use over two hours was 61% (95% CI: 35.9–86.2), a difference users perceived in reduced wetness (10/11), including a 64% mean leakage reduction among the five participants with previous surgical attempts. Acceptability was high; women could easily insert (8/11), remove (8/11), and comfortably wear (11/11) the cup, and most (10/11) would recommend it. No adverse effects attributable to use of the cup were observed on gynecological exam. The data collection tools (e.g., pad test and questionnaire on perceived reduction of leakage and acceptability) were appropriate and easily implemented in the local context. These findings suggested robust evaluation of short and long-term effectiveness is warranted along with continued evaluation of user acceptability, including how use of the cup could supplement or replace existing coping strategies [4, 39, 40].

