#### Observed leakage

Minimum difference was estimated from our efficacy study plus expert clinical opinion as the minimum clinically significant leakage reduction from pad test [24]. Analytical sample size was calculated at 50 using an ANCOVA model with a 2-tailed, alpha error = 0.025 to obtain statistical power of 0.8–0.9.

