#### Stopping rules

Criteria for stopping for harm or significant concerns about safety (e.g., life-threatening or results in death, hospitalisation or prolongs existing hospitalization, results in disability or incapacity, congenital anomaly or birth defect) or observed treatment effectiveness include: a statistically significant difference (*p* < 0.001) according to the Haybittle–Peto boundary. Serious adverse events (SAEs) will also be monitored continuously during data entry, and they will be reported to the DSMB and IRBs. Preliminary analyses will be done by the study statistician, who is unblinded and presents unblinded interim analyses to the DSMB, according to predetermined stopping rules. Recommendations to stop or alter the design or conduct of the trial will be done by the DSMB in instances of high effectiveness and/or poor adherence or unacceptable side effects that can be attributed to the study intervention following pre-determined stopping rules and criteria. Safety reviews will look at both anticipated and unanticipated adverse events. In case DSMB recommends stopping the trial early, a meeting will be held between the study investigators and the DSMB to decide on the trial discontinuation. In case of disagreement, the advice of independent external experts will be sought. A report will be submitted to Korle Bu Teaching Hospital Ethical Committee, Ghana Food and Drug Administration, Amref Research and Ethics and Scientific Review Committee, and UCSF Human Research Protection Program as soon as possible and not later than 10 working days.

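### One p < 0.001 Haybittle–Peto boundary covers both benefit and harm at 50 participants: on 6-hour leakage against free leakage it is almost sure to be crossed, while for serious harm it is practically out of reach

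*Protocol article*

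**What the plan says.** In the Protocol article, Data and safety monitoring sets one formal interim analysis. It is placed midway through clinic-phase data collection, which the same sentence equates with the point "when 50 study participants have completed the study". The section then adds: "Interim analysis of efficacy data when about half the study events are recorded". It describes this look as "using stringent rules for stopping the trial early in case of positive effect".

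Stopping rules supplies the boundary. A single sentence opens with "Criteria for stopping for harm or significant concerns about safety", lists outcomes such as death, hospitalisation and disability, adds observed effectiveness, and gives as the criterion "a statistically significant difference (*p* < 0.001) according to the Haybittle–Peto boundary". No endpoint, comparison or sidedness is attached. Later in the paragraph, high effectiveness, poor adherence or side effects judged unacceptable are named as grounds for a board recommendation.

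The sample-size section on observed leakage states: "Analytical sample size was calculated at 50 using an ANCOVA model with a 2-tailed, alpha error = 0.025 to obtain statistical power of 0.8–0.9". The design effect is a 65% reduction at 6 hours, presented as the minimum clinically significant reduction. The analysis section names percentage change in leakage at 6 hours as the primary outcome variable and lists three primary comparisons: each device against leaking freely, and cup against cup+.

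**The concern.** A Haybittle–Peto boundary is stringent when the interim carries part of the information and the effect is uncertain. Neither holds for leakage here. The look falls at the full calculated leakage sample, and a device that collects urine is compared with no device at all. The boundary also tests only for a difference from zero, not for the 65% reduction that the plan regards as clinically significant.

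A crossing could therefore prompt a recommendation to stop on an almost foregone 6-hour result while the home phase is at about half its planned size. That phase carries 3-month quality of life, longer-term acceptability and cost. Stopping would bring participants little in return, because every woman already uses both devices in the clinic and takes one home.

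For harm the threshold fails in the opposite direction. Few participants and rare serious events make p < 0.001 very hard to reach. At home both arms wear the cup and there is no free-leakage arm, so a harm shared by both devices cannot show as a between-arm difference.

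**Working it through.** **Inputs from the Protocol article.** Feasibility reduction 61%, 95% CI 35.9 to 86.2, 11 women, 2 hours (Background). Baseline leakage 63.2 ml, ± 49.2 read as SD (Quality of life analysis). Design reduction 65%; leakage N = 50, two-sided alpha 0.025. Quality of life: dependent t-test, two-sided 0.05, power 0.85, N = 59, SD of change 28.1.

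**Assumptions not in the document.** Two-sided boundary; 2-hour SD holds at 6 hours; within-person correlation 0 to 0.5; 1:1 home allocation; the event rates used for harm.

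**1. The plan's own figures.**
- Quality of life: a paired t-test with d = 0.40 gives power 0.8496 at n = 58 and 0.856 at n = 59, so 59 reproduces exactly.
- Leakage: a two-group ANCOVA, 25 per group, difference 0.65 × 63.2 = 41.1 ml, SD 49.2, alpha 0.025, gives power 0.80 to 0.90 for a baseline correlation of about 0.35 to 0.57. The 50 is therefore reachable, but only with a correlation that the document does not give.

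**2. Benefit, percentage scale.**
- SE = (86.2 − 35.9)/2 ÷ t(0.975, 10) = 25.15/2.228 = 11.29. SD = 11.29 × √11 = 37.4.
- Feasibility study: t = 61/11.29 = 5.40 on 10 df, p = 0.0003. Eleven women already pass p < 0.001.
- At n = 50 the critical t(0.9995, 49) is 3.50, so the smallest crossing reduction is 3.50 × 37.4/√50 = 18.5%.
- Crossing probability (non-central t, 49 df):

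| True reduction | Probability |
|---|---|
| 20% | 0.61 |
| 25% | 0.88 |
| 30% | 0.98 |
| 35.9% (lower confidence limit) | 0.999 |
| 61% | about 1.00 |

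With the SD 1.5 times larger, the probability at 35.9% is 0.84. With the SD doubled, it is 0.98 at 61%.

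**3. Benefit, ml scale, 65% reduction.** SD of the difference = 49.2 × √(2(1 − ρ)); non-centrality = 41.1 × √50 ÷ that SD.

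| ρ | SD of difference | Non-centrality | Crossing probability |
|---|---|---|---|
| 0 | 69.6 | 4.17 | 0.74 |
| 0.25 | 60.3 | 4.82 | 0.90 |
| 0.5 | 49.2 | 5.90 | 0.99 |

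**4. What 25 per home arm gives for quality of life** (two-sample t-test, two-sided 0.05).
- If 40% means d = 0.40: power 0.28 at 25 per arm, 0.42 at 40, 0.51 at 50.
- If 40% means 40 points with SD 28.1 (d = 40/28.1 = 1.42): power 0.999 at 25 per arm.

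**5. Harm.**
- Home phase, 25 vs 25, Fisher exact: 9 vs 0 gives p = 0.0016; 10 vs 0 gives p = 0.0006. Ten against none is the first to cross. Crossing probability is 0.00005 for true rates of 10% vs 2%, 0.011 for 20% vs 2%, and 0.13 for 30% vs 2%.
- Crossover, exact McNemar with all discordance one way: 10 women give 2 × 0.5^10 = 0.00195; 11 give 2 × 0.5^11 = 0.00098. The chance of at least 11 of 50 is 0.009 if 10% of women have the event only on a device, and 0.42 if 20% do.

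**The case against.** A reader might infer that the rule will end the trial before its 3-month question is answered. The text does not go that far. A crossing leads to a board recommendation and then to a meeting of investigators and board, with outside experts if they disagree; the board may also advise carrying on unchanged. Nothing ties the boundary to leakage or to the free-leakage contrast. Cup against cup+ is also a primary comparison, and there crossing is not foregone: with SD 37.4 the probability is 0.07 for a 10-point difference and 0.61 for 20 points. Further detail may sit in a charter or analysis plan that is not shown.

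Nor is the 3-month question necessarily lost. If the 50 have literally completed the study, they already have 3-month data, and 25 per arm is ample for a 40-point difference. Under d = 0.40 even 50 per arm gives only 0.51, so much of that weakness lies in the sample-size basis. The 59 comes from a paired test and is not a like-for-like benchmark for two parallel arms.

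Near-certainty also depends on the scale and on an SD from 11 women over 2 hours, before the valve and leg bag were added. If 50 really carried only 0.8 to 0.9 power at alpha 0.025, crossing p < 0.001 would have probability 0.42 to 0.59. That power fits a two-group comparison, though, not the within-person one planned.

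A reader might also infer that women are unprotected against harm. They are not: the listed criteria are not exhaustive, serious adverse events are monitored continuously, investigators review safety weekly, and the board may act at any time and on unacceptable side effects.

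These points limit the consequence. They do not rescue a shared threshold that gives the board little guidance in either direction. Leakage is the natural reading of efficacy data, because it is the only variable called the primary outcome.

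**Conclusion.** The concern holds in a limited form. One p < 0.001 boundary serves benefit and harm, and the efficacy look comes at the full leakage sample of 50. Applied to device against leaking freely on the stated primary variable, it is nearly certain to be crossed; on the ml scale at the design effect, crossing is likely to very likely. A reduction well under a third of the design effect (18.5/65 = 0.28) would suffice, so the rule is not stringent for this outcome. It could prompt a recommendation to stop with about 25 women per home arm, which would cut short acceptability and cost in any case, and quality of life materially only if 40% means d = 0.40.

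For harm the boundary adds no useful protection for serious or uncommon events, although a common one-way effect in the clinic phase could reach it. Safety oversight by other routes remains in place.

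Separately, the interim is fixed at two different moments: midway through the clinic phase, and 50 women having finished a study with up to 3 months of home use. These cannot both be the trigger.

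The size of the benefit result rests on the feasibility SD, a two-sided boundary and the leakage reading of the rule.

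**What to change.** Amend the interim and stopping-rule paragraphs and the board charter:

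1. State that a leakage crossing at the look at 50 does not stop accrual or the home phase, so that there is no early stopping for leakage benefit.
2. Confine p < 0.001 to efficacy, and name the endpoint and comparison for any efficacy boundary that remains.
3. Reconcile the harm criteria within Stopping rules, so that safety action by the board does not depend on a significance threshold. The clinical content of those criteria is for the investigators and the board.
4. Reconcile the two descriptions of when the interim takes place.

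This adds no participants or procedures. The cost is the option to stop early for leakage benefit, which is small for participants given that all use both devices and take one home. The change should come before unblinded interim data are seen. Whether that is still possible is unknown: Study status reports 16 completers without a date.

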#### Participant removal

Study physicians will consider a participant’s removal from the study if there is harm caused to participant with use of either cup or cup + that prevents their ability to continue using the devices for the planned duration.

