#### Quality of life

Using dependent t-test with 2-tailed, alpha error = 0.05, estimated mean difference of effect between the cup and cup + of 40%, and power 0.85 to avoid type 1 error, required sample size is 59. Estimates of the effect are based on data collected within a longitudinal study of post-surgical fistula repair patients in Uganda, [66] wherein participants were asked about quality of life using the post-repair fistula reintegration measure which is standardized to a range of 0-100 [67]. Participants reported a mean of 36.7 (SD = 19.0) at the time of fistula repair (referring to living with fistula) and a mean of 78.0 (SD = 22.7) at follow up (6 months post-repair), reflecting a mean change of 40.5 (SD 28.1): 54.2 (SD 14.5) among those who were not leaking urine and 13.1 (SD 28.9) among those who continued leaking urine. The cup + is estimated to have a comparable improvement on quality of life as surgical repair, while the cup, based on our observations during our feasibility study [37] and on expert opinion, is estimated to have a smaller effect on quality of life over the long-term (3 months) as it has 1/15th of the capacity for urine storage and thus will need more frequent emptying than the cup+.

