### Community-based procedures

On the last clinic day, participants will be individually randomized to use of cup or cup + at home for up to three months (see Randomization; Fig. 1) for community-based assessment of the longer-term effectiveness, acceptability of the cup and cup+, and material and opportunity costs to non-surgical fistula management. We will assess perceived change in leakage associated with cup/cup + use, quality of life, acceptability and adherence via survey and clinical checklist administered at one and two months either over the phone as we have done in prior studies [63, 74] or in-person per participant and data collector preference, and semi-structured interview and clinical exam in-person at three months. Participants will be provided with airtime to ensure their ability to contact study personnel.

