### Study termination

Participants will be free to discontinue use of any individual intervention assignment or withdraw from the trial completely at any point throughout the study. Criteria for study-initiated discontinuation include user perception of and/or clinical observation of adverse events such as significant pain. Study participation will not delay participant access to fistula surgery; if active study participants are called for fistula surgery, they will complete research activities through the time of surgery at which point they will be withdrawn. Outcomes will be recorded for those who discontinue or deviate from the intervention protocol, including reason for discontinuation or deviation and length of use. Participants will receive a clinical exam at the time of discontinuation or deviation.

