### Data analysis

#### Quantitative

We will assess missingness and normality of variables; multiple imputation (> 5% missingness), transformation and other techniques will be considered. Data will be summarized descriptively. Intention-to-treat will be the primary analysis. Study data management procedures are available upon request by the study team.

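### Harm that stops device use can take a woman out of the study, not only off the device, which fits poorly with the discontinuation rules and with intention-to-treat

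*Protocol article*

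**What the plan says.** Under Data and safety monitoring, Participant removal, physicians will consider a participant's "removal from the study if there is harm caused to participant with use of either cup or cup" (the sentence continues to cup+) that "prevents their ability to continue using the devices for the planned duration".

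Study termination draws a distinction. Women are "free to discontinue use of any individual intervention assignment or withdraw from the trial completely", and adverse events such as significant pain are a ground for the study itself to discontinue use. For such women the section says "Outcomes will be recorded for those who discontinue or deviate from the intervention protocol", with the reason, the length of use and a clinical exam. Its only worked example of withdrawal is a call for surgery, where "they will complete research activities through the time of surgery at which point they will be withdrawn".

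Data analysis, Quantitative states "Intention-to-treat will be the primary analysis". Table 2 schedules quality of life, perceived leakage, acceptability, stigma, symptoms and costs at months 1, 2 and 3. Under Community-based procedures, follow-up is "administered at one and two months either over the phone" or in person, with an in-person visit at three months.

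**The concern.** The same event, harm that makes a woman stop her device, has two consequences in the document. Under Study termination it is a discontinuation with outcomes recorded. Under Participant removal it may end her participation. The surgery example treats withdrawal as the end of research activities. If removal for harm works the same way, her remaining surveys are lost, although she can still answer questions about quality of life, stigma and symptoms without using a device.

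This loss would be caused by treatment and related to outcome, and its rate could differ between cup and cup+. Later results would lean towards women who tolerated their device, and a device that harms more women would be flattered. The Background expects limits to effectiveness to come from acceptability and adherence, so these women are among the most informative in the home phase.

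**Working it through.** **The rules side by side**

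| Section | Trigger | Consequence |
|---|---|---|
| Study termination | Woman stops an assignment, or the study stops it for an adverse event | Outcomes, reason and length of use recorded; clinical exam |
| Study termination | Call for surgery | Research activities up to surgery, then withdrawn |
| Participant removal | Harm prevents continued device use | Removal from the study considered |
| Data analysis, Quantitative | – | Intention-to-treat is primary |

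The first and third rows describe overlapping events. No section says that a woman in the third row continues to month 3.

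**What is not lost.** Data already collected are kept, an exam is given at discontinuation, and serious adverse events are monitored under Stopping rules. The clinic phase loses little: every woman has a baseline leaking-freely value (Study design), and harm from the cup may rule out cup+ as well, since both use the same cup.

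**Power is not the issue.** The removal rule carries no figure of its own. The nearest is the quality-of-life sample size of 59. Reading the 40% as a standardized paired difference of 0.4 (my assumption), with two-sided alpha 0.05, power is 0.850 at n = 58 (0.8496, just short of 0.85) and 0.856 at n = 59, so 59 is reproduced. With 20% loss, 59 / 0.8 = 73.75, or 74, within the planned maximum of 100. The question is therefore bias.

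**What is known about harm.** The feasibility study (Background) saw no attributable adverse effect in 11 users, with leakage measured over two hours. The exact two-sided 95% upper limit for 0/11 is 1 − 0.025^(1/11) = 0.285, about 28%. It says little about three months of home use.

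**Size of the shift.** Let p be the share of an arm removed for harm and d the difference in mean gain between retained and removed women.

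- Mean over all women = retained mean − p × d
- Complete-case mean = retained mean
- Shift = p × d

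The values of p are assumptions, and an arm is taken as about 50 women (half of 100). Two values of d are used:

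- d = 10 points, assumed.
- d = 54.2 − 13.1 = 41.1 points, from the sample-size section on quality of life: "54.2 (SD 14.5) among those who were not leaking urine and 13.1 (SD 28.9) among those who continued leaking urine". This is an upper-end value because it comes from surgery.

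| p | Women of 50 | Shift, d = 10 | Shift, d = 41.1 |
|---|---|---|---|
| 0% | 0 | 0 | 0 |
| 2% | 1 | 0.2 | 0.8 |
| 5% | 2–3 | 0.5 | 2.1 |
| 10% | 5 | 1.0 | 4.1 |

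The cup versus cup+ contrast shifts by the difference between the two arms' values, so it is near 0 if removals are equal.

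**The case against.** The strongest reply is that Study termination already covers this event. Harm that stops use is a discontinuation, outcomes are recorded, and removal is only something physicians will consider. The step from removal to lost surveys is inferred from the surgery example, and surgery differs because it treats the fistula itself. Intention-to-treat concerns analysis by assignment, and nothing says collected data are dropped. Mixed models use all available visits and multiple imputation is considered, so a complete-case shift overstates the problem. The shift is also modest: with the SD of change of 28.1 and 50 women, the standard error of an arm's mean is 28.1 / √50 = 4.0 points, so at 2 to 5% removal the shift is at most about half a standard error. Finally, some acceptability items presuppose current use.

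Much of this stands. It is a tension and not a flat contradiction, its size is unproven, and the point about acceptability items is fair in part. Three things remain:

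- Discretion does not settle what happens after removal, and it lets four sites decide differently on an outcome-related ground.
- Recording outcomes for women who discontinue is not an express promise of follow-up to month 3, and the removal rule points the other way.
- Models and imputation can use earlier scores but cannot observe how a removed woman fares afterwards.

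Nor is this a detail that a condensed article leaves out: the removal rule is written in the text.

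**Conclusion.** The concern holds. A treatment-stopping event is given a study-level consequence, which fits poorly with the separation made under Study termination and weakens the primary intention-to-treat analysis of the home phase. The effect is confined mainly to the month 1 to 3 quality-of-life, acceptability and symptom results; the six-hour leakage comparison is little affected. Its size cannot be established from the document. The figures above rest on assumed removal shares, on either an assumed difference or one taken from surgical patients, and on reading removal as the end of follow-up. If continued follow-up is what the investigators intend, only the wording is at fault. The point is worth correcting because the correction is cheap. Confidence is medium.

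**What to change.** Reword Participant removal so that harm leads to stopping the device concerned, or both devices on clinical judgement, and not to removal from the study. Unless the woman withdraws consent:

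- continue safety follow-up, any leaking-freely pad test still due, and the month 1, 2 and 3 surveys;
- keep all data collected;
- analyse her in her assigned home arm if she has been randomized to one.

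Who should stop a device stays with the clinicians.

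The cost is one sentence and a few surveys that are already scheduled, with months 1 and 2 possible by phone. Study status reports 16 completers of up to 100, so most of the planned sample could still benefit. The downside is that some surveys will describe women no longer using a device, so device use should be reported beside the scores.
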